## Method

This hybrid type 3 effectiveness-implementation trial employs a blocked randomized cohort design with an active comparison control (ACC) condition to provide a rigorous initial test of the efficacy of BASIS-T in authentic elementary school settings (see Additional file 1 for SPIRIT checklist). Schools will be randomized to BASIS-T or ACC conditions (see Fig. 2) and data will be gathered at the teacher/classroom level. There will be two cohorts of participants—one for each of two academic years—and multiple time points of data collection over 18 months across implementation and sustainment phases. Institutional review board approval has been obtained (Additional file 2), which includes plans for de-identification and secure data storage as well as tracking and reporting of adverse events or protocol modifications if needed.

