### Randomization

This study will employ a randomized cluster-blocked cohort design with random assignment at the school level to eliminate the possibility of condition contamination among teachers. Schools will be blocked within the district by a number of teachers participating in the study, school enrollment, % of non-White students, % of students who qualify for free/reduced lunch, and mean teacher baseline BASIS-T mechanisms of change (e.g., self-efficacy). These variables were chosen because they are associated with EBPP use and student academic outcomes [59]. We will create matched pairs using the nearest neighbor approach [60] and randomly assign schools within pairs to condition. Randomization will occur to the greatest extent possible, although there may be some situations where trainers in only one condition are available when school staff are available to be trained; these situations will be considered essentially random. School personnel and participants will be masked to condition.

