#### Active comparison control

Teachers assigned to the ACC will receive pre- and post-training experiences designed to mirror those received in the BASIS-T condition. These training experiences will be virtual (again via Zoom or similar) and approximately the same length as BASIS-T but will not contain any of the BASIS-T content or mechanisms of change. The ACC pre-training experience will define, describe, and advocate for EBPP implementation and fidelity of EBPP use in schools. Content will be delivered in modes that mirror that of BASIS-T with video content, workbooks, and didactic training. The ACC thus controls for dose, information provided, and delivery mode effects. Some trainers will provide ACC and BASIS-T to reduce the potential for trainer effects.

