#### Power

Our planned sample, including attrition, will provide sufficient power to test linear effects on teacher- and classroom school-level variables with a minimum detectable effect size (MDES) of small to medium effects, *d* = 0.37. We used PowerUp! [100] assuming clustering, final samples of 46 schools evenly randomized to condition, 6 teachers per school (after 15% attrition), school ICCs of 0.10 (consistent with our pilot data), and 13 timepoints. With the same assumptions as above, plus an assumption that 50% of the schools will be in a given moderator subgroup, our MDES for detecting any single school-level moderator variable is 0.48 and teacher-level moderator variable is 0.45. For mediator analyses, PowerUp! identifies power using the Sobel test, joint test, and Monte Carlo simulations. Across all tests, we will have a power of greater than 0.80 to detect reasonable and likely effects, based on our pilot trial and standard interpretations of effect sizes. We will detect an MDES equivalent to Cohen’s *d* = 0.60 for the treatment-mediator pathways (e.g., BASIS-T to implementation intention) which is lower than our actual obtained effect size from the pilot trial (which ranged from *d* = 0.61 to 1.16 for our primary mediators), an MDES of Pearson’s *r* = 0.3 for the mediator-outcome path (e.g., implementation intention to student behavior, a small effect), and an MDES of *d* = 0.10 for the direct path from treatment to student outcome.

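### The protocol lets trainer availability decide a school's condition, sets no limit on this, and counts it as random, so every BASIS-T versus ACC comparison is exposed to selection bias of unknown size and direction

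*Protocol article*

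**What the plan says.** The Randomization section of the protocol article sets out the intended scheme: "We will create matched pairs using the nearest neighbor approach [60] and randomly assign schools within pairs to condition". Matching is within district, on the number of participating teachers, school size and composition, and the mean baseline score of teachers on the BASIS-T mechanisms.

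The section then opens an exception: "Randomization will occur to the greatest extent possible, although there may be some situations where trainers in only one condition are available", and the sentence continues "when school staff are available to be trained; these situations will be considered essentially random". It does not say how many schools may be placed this way, what happens to the matched partner, or whether these schools will be identified.

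Elsewhere the exception disappears. The Method section states "Schools will be randomized to BASIS-T or ACC conditions (see Fig. 2) and data will be gathered at the teacher/classroom level". The Power section assumes "final samples of 46 schools evenly randomized to condition". The Abstract and the Limitations also describe randomised schools without qualification.

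Three other provisions bear on the point:

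- The Randomization section says that school personnel and participants are masked to condition.
- The Data analytic plan adjusts for baseline non-equivalence on measured school, teacher and student variables.
- The Active comparison control section says "Some trainers will provide ACC and BASIS-T to reduce the potential for trainer effects".

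**The concern.** Under the exception, a school's condition depends on the overlap between its own calendar and the calendars of trainers for one arm. The dates a school can offer may reflect leadership support, release time and workload. The protocol itself names supportive leadership and implementation climate as possible moderators of effect (Objectives and aims, RQ 2b), and neither is among the matching variables.

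The pairing is affected as well. If one school of a pair is placed by availability, either its partner takes the other condition without a draw, or the pair is broken.

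The Aim 1 contrasts and the Aim 2 mediation, moderation and cost-effectiveness analyses all use the same assignment, so any imbalance reaches all of them. Recruiting more schools would not remove the bias if the affected share stayed the same. Declaring these placements random in advance also means that a reader of the results could not tell which schools were truly randomised.

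**Working it through.** **1. The stated benchmark.** Inputs from the Power section: J = 46 schools, evenly split (P = 0.5), n = 6 teachers per school, school ICC ρ = 0.10. The Data analytic plan gives α = 0.05 without saying whether it is one- or two-sided. Power of 0.80 is assumed for the main effect, because the article states it only for the mediator analyses. No covariates are used.

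SE = sqrt{[ρ + (1 − ρ)/n] / [P(1 − P)J]} = sqrt{(0.10 + 0.90/6) / (0.25 × 46)} = sqrt(0.25/11.5) = 0.147.

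The minimum detectable effect is (t for α + t for power) × SE, with 44 df:

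- one-sided: 2.530 × 0.147 = 0.373, which matches the stated 0.37;
- two-sided: 2.865 × 0.147 = 0.42.

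The bias is compared below with the stated 0.37. The precision cost of the fix uses the two-sided 0.42. The gap between the two figures is a separate matter and does not affect this point.

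**2. Bias formula.** Let a share f of the schools in each arm be placed by availability, and let those schools differ systematically between arms by D teacher SDs on the outcome, for reasons other than treatment. The remaining schools are balanced in expectation, so

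bias = f × D.

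This assumes the same share f in each arm, and D is the imbalance left after any adjustment.

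**3. A plausible scale for D.** At ICC 0.10 the between-school SD is sqrt(0.10) = 0.316 teacher SD. A gap of g school SDs is therefore D = 0.316g. The article gives neither f nor g, so both are assumptions: f from 0.10 to 0.30 (about 5 to 14 of 46 schools) and g from 0.2 to 0.5.

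| f | g (school SDs) | D (teacher SDs) | Bias f × D | Share of 0.37 |
|---|---|---|---|---|
| 0.10 | 0.2 | 0.063 | 0.006 | 2% |
| 0.10 | 0.5 | 0.158 | 0.016 | 4% |
| 0.30 | 0.2 | 0.063 | 0.019 | 5% |
| 0.30 | 0.5 | 0.158 | 0.047 | 13% |
| 0.30 | 1.0 | 0.316 | 0.095 | 26% |
| 0.30 | 1.58 | 0.50 | 0.150 | 41% |

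The last two rows show what a much larger gap would do.

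**4. Effect on the test.** With SE 0.147 and 44 df (noncentral t), a bias of 0.006 leaves the two-sided type I error at 0.050. A bias of 0.047 raises it to about 0.061.

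**5. Precision of an analysis limited to intact pairs.** If 3 of 23 pairs drop out, J = 40, SE = sqrt(0.25/10) = 0.158 and df = 38. The two-sided minimum detectable effect is 2.876 × 0.158 = 0.455, against 0.42 with all 46 schools.

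**The case against.** The strongest reply is that the article says only that such situations may arise, and that several features limit the harm.

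- School personnel and participants are masked, so a school could not knowingly pick dates to obtain an arm.
- A link between a school's dates and its leadership does not by itself favour one arm. Trainer availability would also have to differ by condition in a way that tracks those school traits, and the article describes no such pattern.
- Pairs are matched on baseline mechanisms, measured non-equivalence is adjusted for, and leadership and climate are collected in the surveys.
- Delivery is virtual and some trainers cover both conditions, so the exception may be rare.

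Much of this stands. A reader might infer that the clause certainly biases every estimate and invalidates the p-values, or that the bias could reach 40% of the detectable effect. The documents do not support either inference. A figure near 40% needs about 30% of schools and a gap of 0.5 teacher SD, which is 0.50/0.316 = 1.58 between-school SDs, with nothing removed by adjustment. Nor do the documents show that whoever does the scheduling knows the condition attached to a slot, because they do not say who schedules.

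The allocation rule itself is not rescued. Adjustment reaches measured variables only, and the Data analytic plan removes covariates that do not contribute at p < 0.10. Sharing trainers is aimed at trainer effects, not at allocation. The clause is also an affirmative statement about how schools receive their condition, so it is not a detail that an unseen analysis plan would supply.

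**Conclusion.** The point holds as an uncontrolled risk. The protocol permits an unstated number of non-random placements, declares them random in advance, and elsewhere describes all schools as randomised. The direction of any bias is unknown, and its size cannot be derived from the article.

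Under the assumptions shown (10-30% of schools, equally in each arm, a residual gap of 0.2-0.5 between-school SDs, ICC 0.10) it is about 0.006-0.05 SD, or 2-13% of 0.37. That is modest, and with few affected schools it would be negligible. It becomes substantial only if the gap approaches or exceeds one school SD. The reason to act is less the expected size than the fact that, without a record of the affected schools, nobody could later show that it was small.

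**What to change.** 1. Draw and lock the within-pair allocation after the baseline measures used for matching and before training dates are offered. Then schedule trainers to fit the allocation, using those who deliver both conditions where needed.
2. Delete the clause "these situations will be considered essentially random".
3. Record every school still placed by availability, report the number by arm, and do not describe these schools as randomised.
4. Prespecify an analysis restricted to intact randomised pairs, at least as a sensitivity analysis. Making it the primary analysis is a defensible choice but is not required.

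The cost is a change of wording, a change in the order of scheduling and some rescheduling, which virtual delivery makes easier. The restricted analysis loses some precision: dropping 3 of 23 pairs moves the two-sided, no-covariate minimum detectable effect at 80% power from about 0.42 to about 0.455.

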### Intervention

All participants will receive standard tele-delivered training on PGD from educational consultants with expertise in its implementation and in school-based EBPP training more generally. PGD is a proactive classroom management strategy [61] that takes a prevention-based approach to responding to behavioral needs in the classroom [53]. Research shows that PGD can increase student-level outcomes such as on-task behavior and decrease disruptive behavior [51–53]. PGD was designed to facilitate smoother transitions in the classroom by (a) connecting with each student by greeting them by name, (b) using pre-corrective statements with the entire class to communicate expected behaviors for transitions into the classroom, (c) providing specific pre-corrective statements privately to individual students who have difficulty self-regulating their behavior, and (d) providing specific praise and encouragement to students to reinforce desired behaviors [53].

### Implementation conditions

#### BASIS-T strategy

##### BASIS-T motivational components

The BASIS-T implementation strategy integrates three core motivational components (Table 1). First, the BASIS-T facilitator provides strategic education about implementing EBPP and overcoming barriers via maintaining an internal locus of control to improve attitudes. The second component is social influence techniques to alter perceptions of subjective norms, which consists of two broad approaches: (1) social proofing messages using data or testimonials to describe the behavior or attitudes of others and (2) techniques to induce cognitive dissonance. Social proofs have been used to reduce problem behaviors, including alcohol/drug use and disordered eating behaviors [62–64]. Techniques to induce cognitive dissonance operate on the premise that individuals strive for consistency between attitudes and actions [65]. Desired behaviors can be increased by evoking commitments that are active, public (vs. private), and voluntary (vs. coerced) [66]. Third, motivational interviewing (MI) is used to enhance self-efficacy. MI is a collaborative, person-centered approach to elicit and strengthen motivation to change [67]. MI has been adapted as a brief intervention with strong evidence, feasibility, and acceptability among school-based mental health clinicians [68]; shown to improve self-efficacy and implementation among teachers and primary care providers [68, 69]; and used in group contexts to promote change [47]. The BASIS-T facilitator uses group MI techniques by adopting an empathic, non-directive, and person-centered style to elicit self-motivational statements, encourage discussion of potential changes (“change talk”) and enhance self-efficacy.

**Table 1 Tab1:** BASIS-T strategy components

**Motivational components** **(TBP mechanisms)**	**Strategic education (attitudes)**
	Connecting EBPP to student success
	Maintaining an internal locus of control
	**Social influence (subjective norms)**
	Providing normative information
	Testimonials from experts
	Testimonials from similar others
	Evoking public commitments
	**Motivational interviewing (self-efficacy)**
	Elicit-provide-elicit structure
	Professional values clarification activity
	Pros and cons activity to illicit change talk
	Anticipating implementation barriers
	Values-directed goal setting
	“Ruler questions” (e.g., how confident are you)
**Volitional components** **(HAPA mechanism)**	**Action planning and problem-solving planning** **(Maintenance self-efficacy)**
	Action planning to initiate implementation
	Problem-solving planning to overcome barriers

##### BASIS-T volitional components

To address the intention-behavior gap, BASIS-T includes volitional planning interventions to increase the likelihood that teachers will maintain their self-efficacy by enacting specific implementation behaviors associated with an EBPP. These strategies have been shown to help people enact health behaviors they are already motivated to perform [70–75]. Moreover, these planning interventions have demonstrated success in improving teacher adoption of interventions for student behavior [76]. These interventions support the translation of intentions into actions through detailed planning of how to perform desired behaviors in specific contexts. Solutions are generated to situational and internal (e.g., cognitive) barriers to facilitate follow-through with the action plan. In combination, action planning and problem-solving planning increase the likelihood of behavior change [77].

##### BASIS-T structure

BASIS-T is delivered in a group-based format shortly before and after receiving EBPP (e.g., PGD) training. BASIS-T will be delivered via tele-facilitation (via Zoom or another similar video conferencing platform), pre-recorded video content, and electronic sharing of documents to promote scalability. BASIS-T facilitators are experienced school-based professionals. A *pre-training session* (75 min) targets attitudes, social norms, and perceived behavioral control. The pre-training opens with the facilitator engaging teachers in an activity to clarify their professional values (an MI component). The facilitator uses open-ended questions to elicit change talk and reflects, summarizes, and draws themes across participant responses. The pre-training session is designed to help participants (a) explore their professional values and goals and make connections between those and EBPP training opportunities, (b) link EBPP delivery to improved outcomes for students, and (c) recognize common cognitive shortcuts that leave individuals vulnerable to adopting non-EBPPs. Teachers collaboratively develop an individualized menu of potential solutions to implementation barriers from which they can select when encountering challenges and set value-congruent goals related to the upcoming EBPP training.

The BASIS-T *post-training session* (75 min) provides protected time and a structured experience to develop action plans and problem-solving plans. Teachers will be provided with an action planning template to detail what PGD components they will use, how, with whom, where/when, and the environmental cues and resources needed to serve as prompts to deliver PGD with fidelity. The problem-solving plan involves teachers anticipating situational barriers and generating solutions to overcome those barriers to develop personalized “if–then” plans for dealing with specific barriers. Teachers share their plans with colleagues to receive input and feedback and to publicly set values-based goals for implementation.

##### BASIS-T fidelity

The BASIS-T pre- and post-training intervention sessions will be recorded and independently coded by two trained research assistants with disagreements resolved through consensus dialogue [78, 79]. The research assistants will use the BASIS-T fidelity tool [47] to assess the fidelity of its delivery.

#### Active comparison control

Teachers assigned to the ACC will receive pre- and post-training experiences designed to mirror those received in the BASIS-T condition. These training experiences will be virtual (again via Zoom or similar) and approximately the same length as BASIS-T but will not contain any of the BASIS-T content or mechanisms of change. The ACC pre-training experience will define, describe, and advocate for EBPP implementation and fidelity of EBPP use in schools. Content will be delivered in modes that mirror that of BASIS-T with video content, workbooks, and didactic training. The ACC thus controls for dose, information provided, and delivery mode effects. Some trainers will provide ACC and BASIS-T to reduce the potential for trainer effects.

#### Teacher and school data collection

Teacher data collection will span both active implementation and sustainment phases (18 months per cohort). Data will include teacher quantitative web-based surveys and qualitative interviews, each of which will be incentivized. To promote data integrity, key items will be forced to choose to prevent unplanned missingness and out-of-range responses. All data will be de-identified and stored securely. Detailed information about all study measures (including citations) can be found in Additional file 4.

#### Quantitative surveys

Participants will complete secure web-based surveys at 13 timepoints spanning three phases: preparation (times 1–4), active implementation (times 5–11), and sustainment (times 12–13 follow-up during the next academic year) [45]. Time 1 will occur during informed consent, time 2 in the days immediately before BASIS-T/ACC pre-training, time 3 immediately after pre-training, time 4 immediately after post-training, time 5 two weeks after training, time 6 four weeks after training, times 7–11 monthly until the end of the academic year, time 12 at the beginning of the subsequent academic year, and time 13 during the spring of that academic year. Teachers will self-report demographics, perceptions about BASIS-T (when relevant) and PGD training, BASIS-T mechanisms, implementation outcomes, organizational moderators (implementation climate, leadership), and time and resources used for PGD implementation. From times 7–11, to reduce the respondent burden we will use a random item planned missingness design for measures of attitudes (1 item selected per subscale), action self-efficacy (2 items selected), and subjective norms (1 item selected per each scale).

Data collection regarding students will focus on classroom behavior, behavioral discipline, attendance, and academic performance and will be collected in aggregate at the classroom level, without individual identifiers. Teachers will complete the first secure online survey on student classroom behavior at time 4, as earlier data collection would prohibit teachers from having an adequate sample of student behavior. At the end of each school year, academic and behavioral data (attendance, disciplinary actions, grades, and standardized test scores) will be requested for all students who were in classrooms of participating teachers; these data will be obtained in aggregate at the classroom level and no individual identifiers will be provided to the research team.

